### Study sample, recruitment, and eligibility criteria

We aim to enrol 200 adolescents (14–19 years) or young adults (20–24 years). Recruitment will be monitored closely, and where feasible, efforts will be made to maintain balance across age groups. However, achieving exact balance is not a formal requirement of the study design, and recruitment will proceed pragmatically within the target population. Participants will be recruited through established referral pathways from screening programs in Soweto that identify individuals at risk for depression, anxiety, or suicidal ideation using recognized screening tools: the Patient Health Questionnaire-9 (29), and Generalized Anxiety Disorder-7 (30) that are commonly used in this context (31). All referrals will be assessed by a social worker for eligibility. Eligible participants must: (i) reside in Soweto, (ii) be aged 14–24, (iii) score at risk for depression, anxiety, or suicidal thoughts on screening tools, and (iv) have a primary caregiver residing in the same household (for those under 18) who consents to their participation. Exclusions will apply to individuals with severe intellectual disabilities or communication difficulties, or those outside the age range. The inclusion and exclusion criteria can be found in Table 1 below.

**Table 1 T1:** Inclusion and exclusion criteria.

Category	Criteria	Description	Assessment method
Inclusion	Adolescents/youth aged 14–24 years	Defined age range of participants	Self-report with confirmation via ID, birth certificate, or caregiver report
	Living in Soweto	Residence within Soweto, Johannesburg	Self-report and/or local address verification
	Primary caregiver of adolescent is resident in the same household	Caregiver resides in same dwelling and has primary caregiving responsibilities	Self-report from both caregiver and adolescent
	Scored at risk of probable depression and/or anxiety and/or suicide ideation on screening tools	Positive screen on recognized screening tools	GAD-7 (30) score ≥10; PHQ-9 (29) score ≥10; The ‘at risk’ category reflects moderate symptoms reported in the past 2 weeks, consistent with prior studies using these tools to signal probable caseness (29–31)

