#### Staff

To deliver the intervention, a social worker and five certified (national qualification certificate) community health workers (CHWs) will be required. Recruitment of staff will be guided by minimum baseline criteria, including a relevant qualification, at least two years’ experience working with the target population or in a related field, and demonstrated strong interpersonal and reflective practice skills. A 4-week training program, including in-field practice, would be the minimum time required for a psychologist to equip the team to deliver the intervention as outlined in the competency matrix (see Table 2). The team will be trained in an overview of mental health issues, the tenets of the intervention package and activities, distress protocols, self-care practices, and psychological first aid principles. At the end of training, the intervention team will undergo a structured assessment involving observed role-play and reflective discussion to ensure readiness to deliver the intervention. To support the CHWs and social worker, standard operating procedures will ensure uniform delivery of intervention modules. Fidelity to the intervention model will be monitored through regular structured observations using a fidelity checklist, ongoing self-assessment, and monthly supervision by a psychologist. Additional supervision will be available as needed. These quality appraisal and support mechanisms are in place to ensure that the intervention is delivered consistently and effectively.

**Table 2 T2:** Intervention team training in counselling skills.

Counselling skills that can be provided by community health workers	Included in training
Active listening: Teaching CHWs to listen attentively without interrupting, showing empathy, and understanding the participant's concerns and emotions.	✓
Empathy and compassion: CHWs to approach participants with empathy, understanding their emotional and social contexts, and responding in a caring and non-judgmental manner.	✓
Basic mental health support: Providing CHWs with the skills to recognize common mental health issues, offer basic support, and know when to refer clients to professional mental health services.	✓
Motivational interviewing: Training CHWs in motivational interviewing techniques can help them encourage behaviour change in areas like smoking cessation, adherence to medication, and healthy lifestyle choices.	✓

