### Data collection

Participants will serve as their own controls, with the primary outcome being the change in depression or anxiety status from baseline to exit after the 9 sessions. Assuming a 20% reduction in depression or anxiety (Cohen's d = 0.2), a sample size of 200 will provide 80% power. Data will be collected by the CHWs using secure tablets and the REDCap data collection platform will ensure real-time capturing, reporting and quality control (65). This study may provide early indications of the intervention's potential impact, helping to refine hypotheses for the efficacy trial. It will also evaluate whether the assessment measures are valid, reliable, and sensitive to this target population and context. Table 3 outlines the specific implementation data to be collected.

**Table 3 T3:** Implementation data collection.

Domain	Measure	Assessment time point		
		**Pre-assessment** (Before session 1)	**During intervention** (Session 1–Session 8)	**Post-assessment** (After session 8)
Demography	Sociodemographic questionnaire (date of birth; gender; language; relationship status; education; occupation; household assets; food insecurity)	✓	x	x
Medical	Medical questionnaire (prior diagnosis of anxiety, depression, tuberculosis, epilepsy, HIV; on medication for anxiety, depression, tuberculosis, epilepsy, HIV)	✓	x	✓
	WHO functional Impairments Questionnaire (36)	✓	x	x
	Blood pressure	✓	x	✓
Daily functioning	WHO disability assessment schedule 2.0 (71)	✓	x	✓
Tobacco, alcohol, and drug use	Tobacco use questionnaire (72); AUDIT-Questionnaire (73); drug use questionnaire	✓	x	✓
Stressful life events	Adverse childhood experiences questionnaire (74)	✓	x	✓
Anxiety	GAD-7 (30)	✓	x	✓
Depression	PHQ-9 (29)	✓	x	✓
Self-efficacy	Generalized self-efficacy scale (75)	✓	x	✓
Social support	Social support questionnaire	✓	x	✓
Sleep	Pittsburgh sleep quality index (76)	✓	x	✓
Psychological well-being	PSYCHLOPS (77)	✓	✓	✓
Suicide risk	WHO thoughts of suicide questionnaire (36)	✓	✓	✓

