### Process evaluation

Following MRC guidance on process evaluation (61, 62), we will assess implementation feasibility, mechanisms of impact, and context. Implementation feasibility assessment will focus on what is delivered and how, with compliance monitored via logs and discussions, to determine whether recruitment, retention, and implementation strategies are effective in this setting. Fidelity will be evaluated through observations of CHWs during one-on-one sessions by the social worker, while intervention dose will be tracked using diaries to record contact frequency and duration. Process indicators, including recruitment and retention, and indicators of program delivery will also be assessed. To understand the intervention's impact and how it meets the mental health needs of adolescents and young people, the acceptability of the intervention will be explored by focusing on the participants’ experiences. In-depth interviews and focus groups will be conducted with participants, caregivers, and the CHWs delivering the intervention, asking questions based on the seven component constructs of acceptability (66), as detailed in Figure 5 below. In assessing the context, we will aim to identify factors that might act as barriers or facilitators to intervention implementation or effects. These qualitative methods (interviews and focus groups) will be used to further explore specific issues of relevance, in terms of participants’ experiences of B^3^, key issues facing participants and factors influencing implementation.

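### The community health workers who deliver the intervention also collect PHQ-9 and GAD-7, so the uncontrolled primary pre-post change is liable to reporting bias

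*Protocol article*

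**What the plan says.** The Staff section sets out the delivery team: "To deliver the intervention, a social worker and five certified (national qualification certificate) community health workers (CHWs) will be required". Process evaluation confirms the role by referring to "the CHWs delivering the intervention", and shows that the contact is individual: "Fidelity will be evaluated through observations of CHWs during one-on-one sessions by the social worker".

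Under Data collection the same staff are given the measurement task: "Data will be collected by the CHWs using secure tablets". Table 3 lists GAD-7 and PHQ-9 before session 1 and again at the post-assessment. The primary endpoint is defined as "the primary outcome being the change in depression or anxiety status from baseline to exit after the 9 sessions", and there is no comparison group: "Participants will serve as their own controls". Table 1 makes clear that the scales rest on what participants report; the at-risk category "reflects moderate symptoms reported in the past 2 weeks".

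The safeguards described are a fidelity checklist, self-assessment and psychologist supervision (Staff) and REDCap quality control (Data collection). They concern delivery and data capture. None separates a participant's outcome reporting from the team that treated them.

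**The concern.** A pre-post difference cancels a reporting tendency that is the same on both occasions. It does not cancel one that changes between them. Here the participant's relationship with the assessing team does change: at baseline the CHWs are new to the participant, and at exit they are the people who have just provided a nine-week programme. A wish to please the provider, or the provider's own expectation of benefit, could then affect the exit answers more than the baseline answers.

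With a concurrent arm assessed in the same way, part of this could be estimated. In a single group, no analysis can distinguish it from a treatment effect. The study is labelled Phase I. Even so, the article names this change as the primary outcome, bases the sample size on it, and intends it to help refine hypotheses for the later efficacy trial. An inflated estimate could carry over into that planning.

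**Working it through.** **Inputs from the article (Data collection).** N = 200, Cohen's d = 0.2, stated power 80%, participants as their own controls.

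**Assumptions, not in the article.** Two-sided alpha of 0.05; d standardised on the SD of the paired change; a reporting bias b, in the same SD units, of 0 to 0.20.

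**1. Reproduce the stated power.** For a paired comparison, n = ((1.96 + 0.842)/0.2)² = 196.2, so 197 by the normal approximation. With the noncentral t the requirement is 199. At N = 200 the power is Φ(0.2 × √200 − 1.96) = Φ(0.868) = 80.7%, or 80.4% with the t distribution. The stated 80% is reproduced, and the point made here does not affect it.

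**2. Smallest change that would be significant.** The t critical value on 199 degrees of freedom, divided by √200, gives 0.139 SD. The design therefore responds to small shifts, whatever their source.

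**3. Effect of a reporting bias when the true effect is zero.** The probability of a significant result in the direction of improvement is approximately Φ(b × √200 − 1.96). The last column uses the noncentral t.

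| Assumed bias b (SD of change) | Share of planned d = 0.2 | Chance of significant improvement |
|---|---|---|
| 0 | 0% | 2.5% |
| 0.05 | 25% | 10.5% |
| 0.10 | 50% | 29% |
| 0.15 | 75% | 56% |
| 0.20 | 100% | 80% |

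The last row equals the planned power by construction: a bias as large as the target effect is detected as often as the target effect.

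**Limit of the illustration.** The article words the primary outcome as a change in status. A shift in mean score does not translate into a change in status without a baseline distribution, and the article gives none. It gives no SD in scale points either, so the table stays in SD units. It shows how sensitive the design is to reporting bias. It does not estimate the bias.

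**The case against.** **Mode of administration.** The article does not say whether items are read aloud or self-completed, or whether a CHW assesses the participants they treated. A condensed article may leave such detail to the full protocol, and if participants already self-complete, much of the problem goes away. This limits the claim but does not remove it. The article does state who collects the data, and all five CHWs are on the delivery team, so no allocation among them gives an independent assessor.

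**Direction.** A reader might infer that the arrangement is certain to exaggerate improvement, or that bias acts only at exit. The documents support neither. The Introduction says that stigma keeps adolescents from seeking help even when distress is marked. Guarded answers to an unfamiliar CHW at baseline, followed by fuller disclosure once trust exists, would shrink the observed improvement. A bias towards improvement is the more plausible expectation, but it has not been shown.

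**Acceptability.** A reader might also infer that CHWs interview their own participants about acceptability. The text does not say so: "In-depth interviews and focus groups will be conducted with participants, caregivers, and the CHWs delivering the intervention" lists the CHWs among those interviewed and does not name the interviewer. Data management and analysis gives the coding to independent research assistants. This point makes no claim about the interviews.

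**Stakes.** The study is about feasibility and acceptability, promises only early indications, and leaves efficacy to a randomised trial. That is a fair reason to keep the point modest. It does not dispose of it, because the study is powered on this change.

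**Conclusion.** The point holds as a risk to the primary estimate that follows from a stated arrangement: the team that delivers the intervention also collects the participant-reported primary outcome, and no concurrent control exists to absorb a change in reporting. The change is liable to bias, most plausibly towards improvement; direction and size cannot be derived from the document.

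Under the assumptions in the table, a bias of half the planned effect would raise the chance of a spurious significant improvement from 2.5% to about 29%. That figure depends on an assumed bias, an assumed two-sided 0.05 test and standardisation on the change score. Neither the sample size nor the stated power is in question. This is a cheap improvement and does not stand in the way of the study.

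**What to change.** In Data collection, replace CHW collection of PHQ-9 and GAD-7 with private self-completion by the participant on the study tablet, done in the same way before session 1 and at exit. Where a participant needs reading help, use as far as possible a CHW who did not deliver that participant's sessions, and record who assisted. That CHW is still a member of the delivery team, and with five CHWs and a weekly rotation through four stations one may not always be available. Self-completion is therefore the main remedy, and the choice of helper reduces the problem only in part.

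Report the remaining reporting bias as a limitation whenever the change is used to plan the efficacy trial. Leave the existing distress and suicide-risk procedures as they are.

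The cost is rota planning and reading support for some participants. The tablets are already planned, N = 200 is unchanged and no extra staff are needed.

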### Process evaluation

Following MRC guidance on process evaluation (61, 62), we will assess implementation feasibility, mechanisms of impact, and context. Implementation feasibility assessment will focus on what is delivered and how, with compliance monitored via logs and discussions, to determine whether recruitment, retention, and implementation strategies are effective in this setting. Fidelity will be evaluated through observations of CHWs during one-on-one sessions by the social worker, while intervention dose will be tracked using diaries to record contact frequency and duration. Process indicators, including recruitment and retention, and indicators of program delivery will also be assessed. To understand the intervention's impact and how it meets the mental health needs of adolescents and young people, the acceptability of the intervention will be explored by focusing on the participants’ experiences. In-depth interviews and focus groups will be conducted with participants, caregivers, and the CHWs delivering the intervention, asking questions based on the seven component constructs of acceptability (66), as detailed in Figure 5 below. In assessing the context, we will aim to identify factors that might act as barriers or facilitators to intervention implementation or effects. These qualitative methods (interviews and focus groups) will be used to further explore specific issues of relevance, in terms of participants’ experiences of B^3^, key issues facing participants and factors influencing implementation.

**Figure 5 F5:**
[figure not shown]
Acceptability model for *Boikoetliso Ba Boko (B^3^*) prototype.

### Data management and analysis

REDCap will be used for data management and storage to ensure the confidentiality, security, and integrity of the data collected (65). All information collected will remain confidential and will be stored securely at the University of the Witwatersrand and the Developmental Pathways for Health Research Unit, meeting international security and safety standards. Strict security measures including access controls, computer security, data encryption techniques, confidentiality agreements, and staff training are in place. The results of the research will be published and shared during scientific meetings, as well as with policy and practice stakeholders. Any information that identifies people will not be published or made public by the researchers. All data will be presented as group data, rather than individual data.

Descriptive statistics will be used to summarize markers of feasibility, such as fidelity, dose, and reach. Variations between participants in terms of factors such as fidelity and reach will be analyzed at different points in time using detailed modelling. The transcriptions of focus groups will be imported into MaxQDA coding software, where independent, trained research assistants will code, group, and review themes and sub-themes to identify key findings that emerge over the course of the intervention. The quantitative and qualitative analyses will not be used in isolation. Rather, in-depth qualitative data from participants, caregivers, and the intervention team will be triangulated with quantitative monitoring data documenting the delivery of intervention components. Qualitative data will be analyzed thematically using Braun and Clarke's six-phase framework (67), allowing for both inductive and deductive coding aligned with the study's objectives. To ensure robust triangulation, we will adopt a convergent design by comparing themes across data sources and methods to identify convergence, divergence, and complementarity. This process will be guided by established triangulation protocols in qualitative research (68) and principles for managing multiple qualitative data sources (69), thereby enhancing the credibility and depth of the findings.

### Economics

In resource-constrained settings, cost data is crucial for understanding the feasibility of scaling up interventions (5). In this study, cost data will be collected to determine the total cost of designing, starting up, and implementing the prototype. This will include direct costs such as staff time, training, materials, facilities, and operational expenses, captured through financial records and staff time sheets. While we acknowledge that there is no universally accepted method for evaluating cost-effectiveness in such contexts (70), the primary aim of this economic component is to collate cost data that can inform future cost evaluations and guide resource allocation. Rather than assessing cost-effectiveness or economic feasibility directly, we will focus on generating comprehensive cost information that could support future analyses and decision-making around the scalability and sustainability of the intervention.

## Discussion

The development and implementation of B^3^ offers a proactive response to the mental health needs of adolescents and young people, particularly in resource-constrained settings. By adapting evidence-based interventions such as PM+ and integrating innovative components like ‘Brain Gym’ activities and Virtual Reality, the B^3^ prototype aims to provide a holistic and engaging mental health intervention that is based in the community and links to the existing public health system. Grounded in the Global Youth Mental Health framework (35) and including the Wellcome Trust's Active Commission ‘active ingredients’ for effectively treating and preventing anxiety and depression in young people (49), the B^3^ prototype aligns with established best practices, as well as ensures that the intervention is tailored to the specific developmental and contextual needs of adolescents and young people. The inclusion of evidence-based and innovative components within the guidelines of recognized frameworks enhances the credibility and potential impact of B^3^ prototype.

A major strength of this study is our community-driven approach, which involves both a Community Advisory Group and an Adolescent Advisory Group. This collaboration ensures that the intervention is culturally relevant and addresses the unique challenges faced by adolescents and young people. Furthermore, the stigma and treatment gaps that persist in many communities can be addressed by promoting awareness of mental health issues and showcasing effective community-based interventions. The promising evidence from prior adaptations of community-based interventions, including the YouFB in Zimbabwe (25–27), reinforces the potential efficacy of the B^3^ prototype in providing mental health care to adolescents and young people experiencing anxiety and depression, and suicidal ideation.

As a Phase I implementation study, we aim to monitor the impact of the B^3^ prototype rigorously and adaptively throughout its development and implementation. The combination of qualitative and quantitative evaluation methods will provide a comprehensive understanding of the intervention's effectiveness and feasibility. Additionally, this study will monitor the costs associated with the intervention, which is particularly important in resource-constrained settings. By collecting detailed cost data on design, implementation, and delivery, we aim to inform future assessments of economic feasibility and support decision-making regarding the potential for scale-up in similar contexts.

The findings from this study will play a crucial role in informing the development of a Phase II randomized controlled trial protocol aimed at assessing the efficacy, scalability, and sustainability of the B^3^ prototype. Insights gained from this Phase I implementation study can be used to refine the prototype based on participant feedback and data analysis, highlighting how specific components contribute to its overall effectiveness. This feasibility study will also identify potential risks and barriers, ensuring that the larger efficacy trial is both ethically and practically sound. By identifying practical and logistical challenges, such as staffing, technology access, and funding, early on, the study will help prevent costly mistakes in the full-scale trial and allow for more efficient planning. Demonstrating feasibility and acceptability increases the likelihood of securing funding approval and ethical clearance for the larger trial, offering evidence of the intervention's potential for success. Ultimately, fostering long-term resilience and well-being among adolescents and young people requires systemic changes in mental health care, with interventions like the B^3^ prototype leading the way toward more inclusive and responsive services in resource-constrained communities.
